### Statistical justification of the number of inclusions

Assuming a standard deviation of 10 at the lowest oxygen saturation in control group (33), no missing data, and cross-over for 5% of patients, with the two-sided alpha risk set at 0.05, including 950 patients will provide 85% power for detecting an absolute 2-percentage points between-group difference in lowest oxygen saturation (3% difference in FLORALI2 trial (12) and 96 vs 93% in PREVENT study (22)).

### Envisaged degree of statistical significance

The statistical tests will be performed using a significance threshold of 5%.

### Consideration method for missing, unused or invalid data

In case of missing data on primary endpoint, multiple imputations will be realized. No imputation will be realized on secondary endpoints.

### Management of changes made to the initial analytical strategy

No changes to the statistical analysis plan are planned.

### Choice of subjects to be included in analysis

Modified Intention-to-treat (mITT) analyses will be performed. This population will exclude patient with no legal requirement.

Per protocol analyses will also be performed and will exclude patient with failure of ORI capture, failure of ORI recording or ORI<0.6 at the end of the procedure.

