The oxygen reserve index (ORI) is a new oxygenation-monitoring parameter measured continuously and non-invasively using a specific SpO_2_ sensor (Masimo Inc., Irvine, CA). ORI is a relative indicator of partial-pressure-of-oxygen (PaO_2)_ changes in the moderate hyperoxaemia range (17). ORI recording requires no additional intervention by clinicians in charge of the patient. The ORI is a dimensionless parameter that can range from 0.00 (PaO_2_<100mmHg) to 1.00 (PaO_2_>200mmHg). These were only prospective observational studies conducted on small numbers of patients in the context of planned surgery. Reported time intervals between the ORI decline below 0.4 and desaturation were 30 [20-60] seconds (18,19). We recently reported that, in non-hypoxaemic patients, the median time from an ORI fall below 0.4 and an SpO_2_ fall below 97% during apnoea was 81-s [Q1-Q3: 34-146], which is sufficient to allow preventive interventions. We recently observed than in non-hypoxemic patients, ORI decrease below 0.4 with a 81-s [34-146] median time before the SpO_2_ decrease below 97% during apnea which may allow preventive action. Interestingly, a higher ORI value during preoxygenation was independently protective against hypoxemia (20).

To help determine whether ORI monitoring can minimise hypoxaemia during ETI in critically ill patients, we designed a multicentre randomised controlled trial (RCT) to determine whether ORI monitoring is superior over standard care in preventing hypoxaemia.

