## Description and justification of the treatment plan / method under study

### Treatment plan

Monitoring of the SpO2 will be determined at the beginning of the intubation procedure continuously by 2 sensors (local sensor, and Masimo Rad 7) for all patients. All values will be entered into an eCRF. Each sensor will be placed on index, middle and ring fingers of each hand.

Evaluation of difficult intubation and difficult ventilation will be performed in accordance to factors previously validated: This evaluation will be captured in the electronic case report form (body mass index, mouth opening, thyro-mental distance, Mallampati score, snorer, toothless, sleep apnea) according to De Jong *et al* (25).

ETI is performed in both groups according to the protocol outlined below.

(a) Pre-oxygenation is achieved using the device chosen by the doctor in charge of the patient:

- Bag valve mask delivering oxygen at a minimum flow of 60 L/minute for at least 3 minutes (26–28);
- Non-rebreathing (high-concentration) mask delivering oxygen at a minimum flow of 60 L/ minute for at least 3 minutes (28,29);
- Ventilator in NIV mode providing 100% FiO_2_ for at least 3 minutes (12);
- High-flow nasal oxygen device (e.g., Optiflow^®^) delivering oxygen at a minimum flow of 60 L/minute, with 100% FiO_2_, for at least 3 minutes (30,31).

Choice of preoxygenation device will be at physician discretion but Non Invasive Ventilation will be advised in case of oxygen flow > 8l/min to obtain SpO2≥95%. Additionally, apneic ventilation will be also advised (22).

Preoxygenation will be delivered according to protocol defined with each local primary investigators. Cut-off of 0.6 for ORI objective at the end of the preoxygenation was adopted according to re-analysis of previous data (personal data, not published).

[figure not shown]

(b) Anaesthesia is then induced by injecting a hypnotic agent and a neuromuscular blocking agent. The type and dosage of these drugs is at the discretion of the doctor performing the intubation. Nevertheless, in agreement with international (7) and French guidelines (8), the following two principles are applied:

- The preferred neuromuscular blocking agent in the absence of contra-indications (e.g., hyperkalaemia, burn injury more than 24 hours earlier, spinal lesion, or allergy) is succinylcholine in a dosage of 1 mg/kg. The alternative is rocuronium 1 mg/kg, provided the antidote sugammadex (16 mg/kg) is available.

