- If possible, the hypnotic agent is either hypnomidate 0.2-0.3 mg/kg or ketamine 1-2 mg/kg.

(c) Laryngoscopy is performed using the device choose by physician in charge. The size of endotracheal tube and the size of the Macintosh laryngoscope were chosen by the physician at bedside.

(d) ETI is then performed. The cuff of the endotracheal tube is inflated and the tube is connected to the ventilator. If this first ETI attempt fails, the doctor chooses between a second laryngoscopy and an alternative ETI technique. Alternative ETI technique will be chosen at physician discretion and in accordance to French guidelines (7). Each introduction of the laryngoscope into the oral cavity of the patient is considered a separate laryngoscopy attempt. Use of Sellick’s manoeuver [pressure applied to the cricoid cartilage] during ETI is at the discretion of the doctor in charge of the patient and is recorded in the electronic case-report form [eCRF]. Intra-tracheal tube position is confirmed by analysing the capnography curve over four or more breathing cycles. Total ETI duration is defined as the time from anaesthesia induction initiation to observation of the first inflection on the expired capnography curve (confirming intra-tracheal tube position). All items of electronic case report form were analysis on real time by a third person not in charge of patient’s care.

During intubation procedure, blinded continuous monitoring of SpO2 and ORI (for control group) will be performed by appropriate monitor (Masimo Rad7) with data extraction at regular intervals. Oxygen saturation will be tracked during ETI by research nurse or assistant nurse dedicated to fill the eCRF. ORI evolution will not be provided to investigators in the standard of care group. In the control group, local continuous monitoring of SpO2 will be performed with local pulse oximeter device.

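### The per-protocol set excludes patients by the ORI they reached, which is a result of the assigned strategy and not a deviation from it

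*Protocol*

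**What the plan says.** Protocol section 7.2, Choice of subjects to be included in analysis, names two sets. "Modified Intention-to-treat (mITT) analyses will be performed", and per-protocol analyses are added which leave out patients with "failure of ORI capture, failure of ORI recording or ORI<0.6 at the end of the procedure". No arm is named.

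Four other places bear on this rule:

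- Section 6.2, Treatment plan, makes 0.6 the target of the strategy, at a different moment: "Cut-off of 0.6 for ORI objective at the end of the preoxygenation was adopted".
- The same section has ORI recorded in controls but hidden: "blinded continuous monitoring of SpO2 and ORI (for control group) will be performed", and "ORI evolution will not be provided to investigators in the standard of care group".
- Section 1.1, Positioning of the study, reports from the earlier observational study that "a higher ORI value during preoxygenation was independently protective against hypoxemia".
- Section 2.1 sets the primary outcome window from first laryngoscopy to two minutes after successful intubation.

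**The concern.** A per-protocol set is meant to keep patients who received what they were allocated. A patient in the ORI arm who was monitored exactly as planned and stayed below 0.6 has not deviated; the strategy missed its target in that patient. Removing such patients selects on a variable measured after randomisation, which the intervention is meant to raise and which the protocol regards as prognostic. The groups left are no longer those formed by randomisation.

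The direction of the bias depends on something the text leaves open. If the rule is applied to the ORI arm only, that arm loses its poorer-prognosis patients and gains an advantage. If it is applied to both arms, which the hidden control recordings allow, and monitoring does raise ORI, controls are cut more heavily. The remaining controls are then the better-prognosis ones, and the effect shrinks.

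The time point adds a further doubt. Read literally, the end of the procedure lies in or after the primary outcome window. Sections 1.1 and 3.1 put ORI at 0.00 when PaO2 is below 100 mmHg, so on that reading a patient who is still poorly oxygenated would be excluded partly because of the outcome itself.

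What is at stake is a supportive result that could appear to confirm or contradict the main one for reasons unrelated to treatment.

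**Working it through.** **Inputs from the protocol** (section 7.2, Statistical justification of the number of inclusions, and Randomisation): SD 10, target difference 2 points, two-sided alpha 0.05, 950 patients, 85% power, "cross-over for 5% of patients", 1:1 allocation (475 per arm).

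**Inputs assumed**, because the protocol does not give them: the correlation r between continuous ORI and lowest SpO2, and the share p of each arm that falls below 0.6.

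**1. The plan's own figure.** n per arm = 2 × (1.960 + 1.036)² × 10² / 2² = 449, so 898 in total. Then 898 / 0.95 = 945.3, rounded up to 946, against 950 stated. With 475 × 0.95 patients per arm, power is 85.2%. The stated design reproduces, and the per-protocol rule plays no part in it.

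**2. Selection model.** Take ORI and lowest SpO2 as bivariate normal and keep only patients above the cut. The mean lowest SpO2 of those kept rises by

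r × SD × k(p), with k(p) = φ(z_p) / (1 − p),

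where z_p is the normal quantile at p and φ the normal density. This gives k(0.2) = 0.350, k(0.3) = 0.497, k(0.4) = 0.644, k(0.5) = 0.798 and k(0.6) = 0.966.

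**3. Rule applied to the ORI arm only, no true effect.** False gain = 10 × r × k(p). In brackets is the share of 4,000 simulated trials that were significant at 5%.

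| r | 30% excluded | 40% excluded |
|---|---|---|
| 0.2 | +0.99 (30%) | +1.29 (42%) |
| 0.3 | +1.49 (56%) | +1.93 (75%) |
| 0.4 | +1.99 (82%) | +2.58 (94%) |

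With weak correlation and few exclusions the gain is small: +0.19 at r=0.1 with 10% excluded.

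**4. Rule applied to both arms, true effect +2.** Bias = 10 × r × [k(p in ORI arm) − k(p in controls)].

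- 40% against 60% excluded: 0.644 − 0.966 = −0.322. The bias is −0.64 at r=0.2 and −1.29 at r=0.4, which leaves +1.36 and +0.71.
- 20% against 50% excluded, r=0.4: 0.350 − 0.798 = −0.448. The bias is −1.79, which leaves +0.21.
- Equal shares excluded: the two terms cancel and the bias is 0.

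**5. Time points side by side.** The target in section 6.2 is set at the end of preoxygenation, before laryngoscopy. The exclusion in section 7.2 is set at the end of the procedure, a term that section does not define. The two would agree only if the procedure meant preoxygenation.

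**The case against.** The strongest reply is that little rests on this analysis. The mITT analysis is named first, the per-protocol analysis is an addition, and no decision rule in the protocol depends on it. That stands, and it limits the severity.

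A reader might infer that the per-protocol result will be biased by as much as the 2-point target, creating or erasing the whole effect. The protocol does not support that. It gives the direction of the link between ORI and hypoxaemia, but neither its strength nor the share of patients below 0.6. The false gain needs an ORI-arm-only reading that the text does not state. On the both-arms reading, 40% against 60% excluded shrinks a true +2 without erasing it; coming close to zero takes more unequal exclusion. Nor would conditioning on ORI at the end of preoxygenation remove every benefit, because sections 1.1 and 1.2 also describe early warning during the procedure. The normal model ignores the ceiling of SpO2 at 100%.

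It may be said that the end of the procedure loosely means the end of preoxygenation. That is possible, so the mismatch is a conflict to reconcile and not a proven error. It is also tempting to equate the 5% cross-over with controls who were shown their ORI. The protocol defines neither the nature nor the direction of that cross-over.

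Finally, section 7.2 plans a data review before database freeze to classify deviations and define the analysis sets. That could deal with cross-overs. It does not cure a criterion the protocol already fixes in words, and it leaves the choice of arm to be made late in an open-label trial.

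**Conclusion.** Wrong as written; it should be fixed. The criterion selects on an achieved, prognostic, post-randomisation value, and it states neither the arm nor a time point consistent with the treatment plan. That conclusion rests on the text alone and needs no assumption.

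The size does rest on assumptions. For r between 0.2 and 0.4 in the normal model, the bias is about +1.0 to +2.6 points with 30-40% excluded in the ORI arm only. It is about −0.6 to −1.3 points with 40% against 60% excluded, and about 0 with equal exclusion. Bias of the size of the target is therefore possible but not established. The damage is confined to the supportive per-protocol analysis.

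**What to change.** - Delete the criterion based on ORI below 0.6 from the per-protocol definition.
- Define the set by delivery of the allocated strategy: patient eligible; ORI displayed in the ORI arm and not displayed in controls. Cross-overs in either direction are then excluded.
- If failure of capture or recording stays as a criterion, judge it alike in both arms, using the blinded control recordings. Requiring a usable signal in the ORI arm only would itself be a one-arm exclusion after randomisation.
- Report by arm the share with ORI of at least 0.6 at the end of preoxygenation, as a descriptive process measure.
- Reconcile the time points in sections 6.2 and 7.2.

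The cost is wording in the protocol, carried into the analysis plan. ORI is already recorded in both arms, so this criterion needs no new measurements; whether ORI was displayed as allocated must be identifiable for each patient. The change should be made before any comparison by arm is seen, so that it cannot look driven by results.

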### Randomisation

Randomization will be stratified by centre and expert or non-expert intubator status (experts: ≥5 years’ ICU experience, or ≥ 1 year ICU experience plus ≥2 years’ anaesthesiology training), preoxygenation devices (NIV, others).

It will be performed according to a 1:1 ratio and will be carried out in blocks.

The randomization will be performed under Ennov Clinical by connecting to the website: https://nantes-lrsy.hugo-online.fr/CSonline. The connection will be done with a login, a password and a study number, delivered by the data manager of the Research Unit of the CHU Nantes. The following information must be filled in:

- First initial of the name,

- First initial of the first name,

- Month and year of birth,

- Compliance with the inclusion and non-inclusion criteria (yes/no).

Randomization will be performed by the investigator after confirmation of the possibility of inclusion in the study. The inclusion number will be assigned automatically during randomization. An e-mail confirmation will be sent to the person who performed the randomization and to all the persons concerned.

The randomization list will be made by the statistician in charge of the study. An explanatory guide to randomization will be available online under Ennov Clinical.

# Adverse event vigilance and management

As the protocol is with minimal risks and constraints, no adverse event associated with this study is expected.

The onset of an Adverse Reaction associated with patient care in the course of this protocol shall be reported in the suitable vigilance system (pharmacovigilance, biovigilance, haemovigilance, medical device vigilance, etc.).

# Administrative and regulatory aspects

## Source data and document access rights

Each person's medical data shall only be provided to the sponsor or any person duly authorised by the sponsor, and, where applicable, to authorised health authorities, in confidential conditions.

The sponsor and the supervisory authorities may request direct access to medical records for the purposes of verification of the procedures and/or data in respect of the clinical trial, within the limits authorised by the legislation and regulations.

The data compiled during the trial may be processed electronically in compliance with CNIL requirements.

## Trial monitoring

Monitoring shall be carried out by the Research Division Promotion Department. A Clinical Research Associate (CRA) shall visit each site (investigator and dispensary) regularly to conduct quality control on the data reported in the case report forms.

The protocol has been classified according to the estimated level of risk for the person taking part in the study. It shall be monitored as follows: Risk B: foreseeable risk similar to that of standard care

The on-site monitoring visits shall be organised after making arrangements with the investigator. The CRAs should be able to consult on each site:

- the enrolled persons' data compilation records,

- the patients' medical and nursing files,

- the investigator file,

- the distribution and storage site of the experimental product

## Inspection / Audit

Within the scope of this study, an inspection or audit may be conducted. The sponsor and/or participating centres should be able to provide inspectors or auditors with access to the data.

## Ethical considerations

### Written informed consent

The investigator agrees to provide the subject with clear and precise information about the protocol and request from him/her a written consent. The investigator shall give the subject a copy of the information form and consent form. The subject can only be enrolled in the study after reading the information form and giving his/her written consent form, after taking time to reflect on the matter.

The investigator shall also sign and date the consent form. Both documents should be issued at least in duplicate hard copy format so that the person and the investigator can each keep a copy. The investigator's original shall be placed in the investigator file. If the consent form is signed in duplicate, the investigator keeps the original and gives the copy to the subject.

For patients unable to give consent at the time of inclusion due to impaired consciousness, their next of kin will be given full and honest information, delivered in easily understandable terms, about the study objectives and their right to refuse their relative's participation in the study or to withdraw their relative from the study at any time. Information and informed consent documents created specifically for the study will be given to the next of kin. The participant will be informed as soon as possible and consent will be sought for possible continuation of the research if capacity to consent is restored.

The investigator will also sign and date the consent form and give a copy of the information and consent forms to the patient or next of kin. At least two hard copies of both documents should be issued so that the patient or next of kin and the investigator can each retain a copy.

### Emergency consent form collection

If the family member is not present, it will be derogated to the consent collection obligation at the time of inclusion. This request will be appreciated by the Ethics Committee (EC). Patients for whom no relative is available to receive information and consent to study participation within a timeframe compatible with the study design, will be included in the study after a statement from the physician in charge of the patient confirming that the patient is not available to receive the information, that the situation is an emergency and that no family member is present. Informed consent will be sought from the relative as soon as possible and then from the patient as soon as he or she recovers decision-making competency.

### Ethical Review Board

The sponsor undertakes to submit the draft study to the Ethical Review Board (ERB) for prior approval.

## Registration/INFORMATION with the competent authorities

This protocol shall be the subject of an ANSM information.

## Amendments to the protocol

Requests for substantial modifications should be addressed by the sponsor for notification to ANSM and/or the Ethical Review Board concerned in compliance with the applicable law and its implementing decrees.

The amended protocol should be a dated updated version.

The information and consent forms should be amended if required.

## Study funding and insurance

The sponsor shall fund the study and take out an insurance policy covering the financial consequences of its civil liability in compliance with the regulations.

## Publication rules

Authorship will be granted using the Vancouver definitions and depending on personal involvement and fulfilment of the author’s respective roles. The main publication will report the primary and secondary outcomes. A copy of the publication shall be delivered to Nantes University Hospital, the study sponsor, which shall necessarily be cited. The following statement will also be made in all communications and scientific reports relevant to this study: “This study was supported by a grant from the French Ministry of Health (PHRC-21-0202).

## Source data archiving

The investigator should archive all study data for at least 15 years after the end of the study. At the end of the study, the investigator shall also receive a copy of the data for each person in the investigator's centre sent by the sponsor.

List of appendices

- **Appendix 1: Investigator List**
- **Appendix 2: Summary of Protocol**
- **Appendix 3: Bibliographic references**
- **Appendix 4: Emergency situation attestation form**
- **Appendix 5: Patient information form**
- **Appendix 5bis: Relative consent form**
- **Appendix 6: Relative information form**
- **Appendix 6bis: Relative consent form**
- **Appendix 7: Patient information form, after emergency situation**
- **Appendix 7bis: Patient consent form after emergency situation**
- **Appendix 8: Relative information form, after emergency situation**
- **Appendix 8bis: Relative consent form, after emergency situation**

Appendix 1: Investigator list

Appendix 2: SUMMARY of protocol

| **Title of study** | **Impact of the non-invasive oxygen-reserve-index versus standard of care on periphereal oxygen saturation during endotracheal intubation in intensive care unit: randomised superiority multi-center 2 arms, open trial** |
| --- | --- |
| **Keywords** | Intubation, hypoxemia, intensive care unit, acute respiratory failure |
| **Sponsor of study** | **NANTES University Hospital** |
| **Coordinator**  **(if multi-centre)** | [name] [name]  Médecine Intensive Réanimation  Nantes University Hospital |
| **Number of centres**  **envisaged** | 20 National study |
| **Study duration** | - Total duration:  13 months - Enrolment period: 12 months - Participant treatment period: 1 hour - Participant follow-up period: 28 days |
| **Study type and design** | - Therapeutics - Multi-centre - Controlled, superiority - Randomised - Open label trial, with unified outcome assessment - Prospective |
| **Projected number of cases** | 950 |
| **Study objectives** | Primary objective: The primary objective is to determine whether ORI monitoring increases the lowest oxygen saturation level during the interval between the first laryngoscopy (defined as introduction of the laryngoscope into the mouth) and the end of the second minute after successful ETI.  Secondary objective(s):  - To determine whether ORI monitoring increases the lowest oxygen saturation level according to local oximeter.  - To determine whether ORI monitoring increases the lowest oxygen saturation level according to subgroups.  - To assess safety of ORI monitoring.  - To assess efficacy of ORI monitoring |
| **Study endpoint(s)** | Primary endpoint: lowest oxygen saturation measured by Masimo Rad7 oximeter, during the interval between the first laryngoscopy (defined as introduction of the laryngoscope into the mouth) and the end of the second minute after successful ETI.  Secondary endpoint (s):   - Sensitivity analysis of primary endpoint : - Lowest oxygen saturation, measured by local oximeter, during the interval between the first laryngoscopy. - Sub-group analysis of primary endpoint - Lowest oxygen saturation in pre-defined subgroups   - Body mass index (<30 or ≥30)   - Reason for ETI: hypoxaemia/other   - Shock/No shock at inclusion   - Difficult intubation (yes or no)   ORI threshold (<0.6 or ≥0.6) Safety outcome:   - Occurrence of at least one severe life-threatening complication: death, cardiac arrest, arterial systolic pressure <90 mmHg, and/or SpO_2_<80% and occurrence of each one.   - Efficacy outcome   - ICU mortality - 28-day mortalityICU and hospital stay length |
| **Treatment, interventional procedure under study** | ORI monitoring during preoxygenation of patients admitted in intensive care unit who required oxygen supplementation |
| **Comparator (if applicable)** | Standard of care (3 minutes of preoxygenation with device at physician discretion) |
| **Main selection, inclusion, non-inclusion and exclusion criteria** | Inclusion criteria   - ICU admission and need for ETI to allow mechanical ventilation - Need for supplemental oxygen (via any device and at any flow rate) to obtain SpO_2_>97% - Patient or next of kin informed about the study and having consented to participation of the patient in the study (patients with coma are unable to consent). If patient is no competent and no next of kin can be contacted during screening for the study, trial inclusion will be completed as an emergency procedure by the ICU physician, in compliance with French law - Patients affiliated to a social security system   Non-inclusion criteria   - Fiberoptic intubation required according to physician in charge - contra-indications to laryngoscopy (e.g., unstable spinal lesion) - insufficient time to include and randomise the patient (e.g., because of cardiac arrest) - age <18 years - currently pregnant or breastfeeding - correctional facility inmate - under guardianship, curatorship or under protection of justice |
| **Schedule of the various visits and examinations** | \| **Activities** \| D0  (Inclusion visit) \| D1 to D28 \| D28 \| \| --- \| --- \| --- \| --- \| \| Participant information \| X \|  \|  \| \| Consent \| X \|  \|  \| \| Randomization \| X \|  \|  \| \| Previous medical history \| X \|  \|  \| \| Clinical examination \| X \| X \|  \| \| Efficacy and/or safety assessment \| X \| X \|  \| \| Para-clinical examinations \| X \|  \|  \| \| Compliance \| X \|  \|  \| \| Adverse events \|  \| X \| X \| \| Phone contacts \|  \|  \| X \| |
| **Statistical analysis** | Statistical analyses will be performed by a biostatistician from the methodology and biostatistics platform using SAS or R or Stata.  A data review will be carried out before the freezing of clinical trial data bases, and statistical analyses, with the main stakeholders in the study (investigator, CRA, data manager and biostatistician…). The objective of this review will be to take stock of any difficulties encountered during the study, and to classify the different deviations in order to define the analysis populations.  **Description of the groups at baseline**  Baseline characteristics will be studied using descriptive statistics. No statistical tests will be performed.  **Analysis of primary endpoint :**  Lowest oxygen saturation measured using MASIMO oximeter, during the interval between the first and the end of the second minute after successful ETI (32) will be compared between groups using linear mixed-effect regression model to take into account stratification variable (centre as random effect, intubator status (expert or non-expert) as fixed effect).  **Sensitivity analysis of primary endpoint**  The same analysis will be realized using the lowest oxygen saturation measured by local oximeter.  **Analysis of primary endpoint according to subgroup**  Primary endpoint will be analyzed according to pre-defined subgroups variables:   - Body mass index (<30 or ≥30) - Reason for ETI: hypoxaemia/other - Shock/No shock at inclusion - Difficult intubation (yes or no) - ORI threshold (<0.6 or ≥0.6)   **Analysis of secondary endpoints**  All analyses will be adjusted on stratification criterion.   - Occurrence of at least one severe life-threatening complication: death, cardiac arrest, arterial systolic pressure <90 mmHg, and/or SpO_2_<80% and occurrence of each one using logistic mixed-effect regression model. - The rates of death in ICU and at 28 days will be calculated via Kaplan-Meier plots and compared between groups using Cox regression models. - ICU and hospital length of stay will be compared using linear mixed-effect regression models. - Cognitive score evaluated by F-TICS-m will be compared between groups using linear mixed effect regression model. Patients dead at day 28 will be not included on this analysis. |

SUMMARY OF PROTOCOL IN FRENCH

| **Titre de l’étude** | **Impact de l’indice de reserve d’oxygène non-invasif par rapport à la norme de soins sur la saturation périphérique en oxygène pendant l’intubation endotrachéale en unite de soins intensifs : essai randomisé de supériorité à 2 bras, multicentrique et ouvert.** |
| --- | --- |
| **Mots clés** | Intubation, hypoxémie, ICU, insuffisance respiratoire aiguë |
| **Sponsor de l’étude** | **CHU de NANTES** |
| **Coordinator**  **(si multicentrique)** | [name] [name]  Médecine Intensive Réanimation  CHU de Nantes |
| **Nombre de centres envisagés** | 20 centres en France |
| **Durée de l’étude** | - Durée totale:  13 mois - Période d’inclusion: 12 mois - Période de traitement du participant : 1 heure - Période de suivi du patient : 28 jours |
| **Méthodologie de l’étude** | - Thérapeutique - Multicentrique - Contrôlée, supériorité - Randomisé - Ouvert avec évaluation unifiée des résultats - Prospective |
| **Nombre total de patients inclus** | 950 |
| **Objectifs de l’étude** | Objectif principal : Déterminer si la surveillance de l’ORI augmente le niveau de saturation en oxygène le plus bas pendant l’intervalle entre la première laryngoscopie (définie comme l’introduction du laryngoscope dans la bouche) et la fin de la deuxième minute après la réussite de l’ETI.  Objectifs secondaires :   - Déterminer si la surveillance de l’ORI augmente le niveau de saturation en oxygène le plus bas selon l’oxymètre local - Déteminer si la surveillance de l’ORI augmente le niveau de saturation en oxygène le plus bas en fonction des sous-groupes prédéfini - Évaluer la sécurité de la surveillance de l’ORI - Évaluer l’efficacité de la surveillance de l’ORI |
| **Critères d’évaluation de l’étude** | Critère d’évaluation principal : Saturation en oxygène la plus basse mesurée par l’oxymètre Masimo Rad7 pendant l’intervalle entre la première laryngoscopie (définie comme l’introduction du laryngoscope dans la bouche) et la fin de la deuxième minute après la réussite de l’ETI.  Critère(s) d’évaluation secondaire(s):   - Analyse de la sensibilité du critère d’évaluation principal - Saturation en oxygène la plus basse, mesurée par un oxymètre local, pendant l’intervalle entre la première laryngoscopie - Saturation en oxygène la plus basse dans des sous-groupes prédéfinis - Indice de masse corporelle (<30 ou ≥30) - Motif de l’ETI: hypoxémie/autre - État de choc/absence d’état de choc à l’inclusion - Intubation difficile (oui ou non) - Seuil de l’ORI (<0,6 ou ≥0,6) - Résultat de sécurité : Survenue d’au moins une complication grave mettant en jeu le prognostic vital : décès, arrêt cardiaque, pression artérielle systolique <90mmHg, et/ou Sp02<80% et survenue de chacune d’entre-elles - Résultats d’efficacité - Mortalité en USI - Mortalité à 28 jours en USI à l’hôpital sur durée du séjour - Score cognitif moyen à 28 jours entre les deux groupes (F-TICS-m) |
| **Traitement, procedure interventionnelle à l’étude** | Surveillance de l’ORI pendant la préoxygénation des patients admis en unite de soins intensifs et nécessitant une supplementation en oxygène |
| **Comparateur (si applicable)** | Soins standard (3 minutes de préoxygénation avec un dispositif à la discretion du médecin) |
| **Critères d’inclusion et de non-inclusion** | Critères d’inclusion:   - Admission en unite de soins intensifs et nécessité d’intubation pour permettre une ventilation mécanique - Nécessité d’un apport supplémentaire d’oxygène (par n’importe quell dispositif et à n’importe quel débit) pour obtenir une SpO2>97% - Patient ou proche parent informé de l’étude et ayant consenti à la participation du patient à l’étude (les patients dans le coma sont incapables de donner leur consentement). Si le patient est inapte et qu’aucun proche ne peut-être contacté au moment de l’inclusion dans l’étude, l’inclusion dans l’essai sera réalisée par procédure d’ urgence par le médecin de l’unité de soins intensifs, conformément à la loi française - Patients affiliés à un régime de sécurité sociale   Critères de non-inclusion:   - Intubation par fibroscopie nécessaire selon le médecin responsable - Contre-indications à la laryngoscopie (par exemple, lésion spinale instable) - Délai insuffisant pour inclure et randomiser le patient (par exemple, en raison d’un arrêt cardiaque) - Âge <18 ans - Grossesse ou allaitement - Détenu dans un établissement pénitentaire - Sous tutelle, curatelle ou sous protection de la justice |
| **Calendrier des différentes visites et examens** | \| **Activities** \| J0  (Inclusion visit) \| J1 to J28 \| J28 \| \| --- \| --- \| --- \| --- \| \| Information aux participants \| X \|  \|  \| \| Consentement \| X \|  \|  \| \| Randomisation \| X \|  \|  \| \| Antécédents médicaux \| X \|  \|  \| \| Examens cliniques \| X \| X \|  \| \| Évaluation de l’efficacité et/ou de la sécurité \| X \| X \|  \| \| Examens paracliniques \| X \|  \|  \| \| Compliance \| X \|  \|  \| \| Effets indésirables \|  \| X \| X \| \| Appels téléphoniques \|  \|  \| X \| |
| **Analyses statistiques** | Les analyses statistiques seront réalisées par un biostatisticien de la plateforme méthodologique et biostastitique utilisant SAS ou R ou Stata.  Une revue des données sera réalisée avant le gel des bases de données des essais cliniques et des analyses statistiques, avec les principaux acteurs de l’étude (investigateur, ARC, data manager et biostatistician, …). L’objectif de cette revue sera de faire le point sur les difficultés rencontrées au cours de l’étude, et de classer les différentes deviations afin de définir les populations d’analyse.  **Description des groupes au départ**  Les caractéristiques de base seront étudiées à l’aide de statistiques descriptives. Aucun test statistique ne sera effectué.  **Analyse du critère d’évaluation principal**  La plus faible saturation en oxygène mesurée à l’aide de l’oxymètre MASIMO, pendant l’intervalle entre la première et la fin de la deuxième minute après une ETI réussie (32) sera comparée entre les groupes à l’aide d’un modèle de regression linéaire à effects mixtes pour prendre en compte la variable de stratification (centre comme effet aléatoire, statut de l’intubateur (expert ou non-expert) comme effet fixe).  Analyse de sensibilité du critère d’évaluation principal  La même analyse sera réalisée en utilisant la saturation en oxygène la plus basse mesurée par un oxymètre local.  **Analyse du critère d’évaluation primaire en fonction des sous-groupes**  Le critère d’évaluation primaire sera analysé en fonction des variables des sous-groupes prédéfinis :   - Indice de masse corporelle (<30 ou ≥30) - Motif de l’ETI : hypoxémie/autre - État de choc/absence d’état de choc à l’inclusion - Intubation difficile (oui ou non) - Seuil ORI (<0,6 ou ≥0,6)   **Analyse des critères d’évaluation secondaires**  Toutes les analyses seront ajustées sur le critère de stratification.   - Survenue d’au moins une complication grave menaçant le prognostic vital: décès, arrêt cardiaque, pression artérielle systolique <90mmHg, et/ou SpO2<80% et survenue de chacune d’entre-elles à l’aide d’un modèle de regression logistique à effets mixtes - Les taux de décès en reanimation et à 28 jours seront calculés à l’aide de diagrammes de Kaplan-Meier et comparés entre les groupes à l’aide de modèles de regression linéaire à effets mixtes - Le score cognitive évalué par F-TICS-m sera comparé entre les groupes à l’aide d’un modèle de regression linéaire à effets mixtes. Les patients décédés au 28ème jour ne seront pas inclus dans cette analyse |
